**Methods and analysis:**

In this multimodal neuroimaging randomized trial, a total of 96 female MWoA participants and 30 female healthy controls (HCs) will be recruited. The 96 female MWoA participants will be randomized into three groups: Group A (CAT group), Group B [ipsilateral acupuncture (IAT) group], and Group C (sham CAT group) in a 1:1:1 allocation ratio. Each group will receive 30 min of treatment every other day, three times a week, for 8 weeks, followed by an 8-week follow-up period. The primary outcome is the intensity of the migraine attack. Data will be collected at baseline (week 0), at the end of the 8-week treatment period (weeks 1–8), and during the 8-week follow-up (weeks 9–16). Adverse events will be recorded. Multimodal MRI scans will be conducted at baseline and after 8-week treatment.

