### Clinical outcome measures

#### Primary outcome

The primary outcome is the primary outcome is the intensity of the migraine attack, which will be assessed using a VAS score of 0–10. A headache diary form is designed to record details of each migraine attack, including its cause, duration, intensity, presence of aura, accompanying symptoms, frequency, and whether the migraine attack interfered with daily life and work, or emergency medication taken for unbearable pain. The headache diary form will be completed manually by the patient at the end of each migraine attack and will be monitored regularly by a dedicated researcher, who will collect and evaluate the data every 4 weeks (Supplementary File 4).

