### Clinical data analysis

Statistical analysis will be performed by independent statisticians who will have no knowledge of group allocation or the intervention process. Clinical outcomes will be analyzed using SPSS 28.0 statistical software (SPSS Inc., Chicago, IL, USA). All statistical analyses will adhere to the intention-to-treat principles. The missing data of participants who drop out will be handled using multiple imputation by chained equations (Azur et al., 2011), which can impute mixtures of continuous, binary, unordered categorical, and ordered categorical data. In addition, a per-protocol population analysis will be performed on participants who have completed at least 80 percent of their treatment protocol after randomization. Qualitative data will be presented as percentages [*n* (%)] and compared using the Chi-square (χ^2^) test. Quantitative data will be reported as means ± SDs and IQRs. Shapiro–Wilk tests will be performed to assess the normality of the data. Comparisons among the three groups will be analyzed using one-way analysis of variance (ANOVA), and non-parametric tests will be employed when the distribution is not normal. Outcomes will be analyzed using a one-way repeated measures ANOVA to evaluate the impact of time, group, and time × group interactions on migraine attacks. Comparisons of categorical data among groups will be examined using χ^2^ tests or Mann–Whitney U tests. All hypothesis tests will be two-tailed analyses, with statistical significance determined by a *p*-value < 0.05.

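### The clinical repeated-measures model is mislabelled as one-way, and the stated between-group test leaves the collected baseline VAS unused, which costs precision but not validity

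*Protocol article*

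**What the plan says.** The primary outcome is the "intensity of the migraine attack, which will be assessed using a VAS score of 0–10", taken from the headache diary. The Abstract states: "Data will be collected at baseline (week 0), at the end of the 8-week treatment period (weeks 1–8"), and again during follow-up. Table 1 shows the diary at weeks −4, 0, 4, 8, 12 and 16.

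The Clinical data analysis section gives two methods for quantitative outcomes:

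- Between arms: "Comparisons among the three groups will be analyzed using one-way analysis of variance (ANOVA"). A non-parametric alternative applies if normality fails.
- Over time: "Outcomes will be analyzed using a one-way repeated measures ANOVA to evaluate the impact of time, group". The sentence goes on to name the interaction of the two as a third effect.

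No covariate is named for any clinical outcome. Testing is two-sided at 0.05.

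The Neuroimaging data analysis section describes the same three-arm design with a two-factor mixed ANOVA of time and treatment, followed by paired tests within each arm. It lists covariates for the voxel-based morphometry comparison.

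The first aim in the Introduction is to compare CAT with sham CAT and with IAT.

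**The concern.** The label and the stated purpose of the repeated-measures analysis do not match. Taken literally, the named model lacks the two terms that concern treatment, so an analyst must substitute another model. It is better to name that model before the data are seen.

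The between-arm test that can be run as written ignores a baseline measurement that every patient has. This gives away precision in a trial whose arm size of 30 rests on imaging reproducibility, with no effect size, SD or power stated for the VAS in the Sample size calculation section.

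**Working it through.** **Inputs from the protocol article.** Three arms, 1:1:1; 30 patients per arm, recruited as 32 to allow for 8% loss; two-sided alpha 0.05; VAS measured at baseline; entry limited to 3 < VAS < 7.

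**Assumed input.** The article gives no baseline-to-post correlation ρ. I use 0.3, 0.5 and 0.6.

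**The plan's own figure.** 30 × 1.08 = 32.4 and 30/0.92 = 32.6, so 32 per arm is reproduced to within one patient. No clinical power is stated, so there is none to reproduce.

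**Check 1: what a one-way repeated-measures model contains.** Its terms are patient and time. For 90 patients and T time levels the rank is 90 + T − 1.

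- With T = 5 (weeks 0, 4, 8, 12 and 16, an assumption) the rank is 94.
- Adding group leaves it at 94, because arm is constant within a patient and is absorbed by the patient terms.
- Adding time by group raises it to 102. These are (3 − 1)(5 − 1) = 8 degrees of freedom that the one-way model does not have.
- With T = 3 (weeks 0, 4 and 8) the interaction would have 4. The article does not say which levels enter, but the mismatch is the same for any T.

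A mixed design with group between patients and time within patients supplies both terms. With T = 5, group has 2 and 87 df, and time by group has 8 and 348.

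**Check 2: what baseline adjustment is worth.** Compare two arms at one post-baseline window, with the post-treatment SD set to 1.

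- Variance ratio, adjusted to unadjusted: 1 − ρ².
- Equivalent unadjusted arm size: 30/(1 − ρ²).
- Difference detected with 80% power by the adjusted contrast (normal approximation): (1.960 + 0.842) × √(2/30) × √(1 − ρ²) = 0.723 × √(1 − ρ²).
- Power of the unadjusted pairwise test at that same difference: Φ(2.802 × √(1 − ρ²) − 1.960).

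| ρ (assumed) | Variance cut | 30 per arm acts like | Difference (SD) | Adjusted power | Unadjusted power | Loss (points) |
|---|---|---|---|---|---|---|
| 0.3 | 9% | 33 | 0.69 | 80% | 76% | 4 |
| 0.5 | 25% | 40 | 0.63 | 80% | 68% | 12 |
| 0.6 | 36% | 47 | 0.58 | 80% | 61% | 19 |

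**Check 3: does a mixed ANOVA with baseline as a time level do the same job?** Its interaction compares changes from baseline. A simple change score has variance 2(1 − ρ): 1.40, 1.00 and 0.80 at ρ = 0.3, 0.5 and 0.6. Covariate adjustment gives 0.91, 0.75 and 0.64. So correcting the label alone would not recover the precision, and below ρ = 0.5 a change score is less precise than the post-treatment score alone.

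**The case against.** The case against is substantial, and much of it stands.

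- **The label is a slip.** The sentence itself lists group and time by group, and the imaging section names the right design. A reader might infer that the primary analysis cannot deliver the treatment comparison. The documents do not support that: the intended mixed ANOVA is workable, and an ANOVA does not prevent follow-up contrasts.
- **Lack of adjustment is not bias.** Randomisation keeps the unadjusted comparison unbiased. An unseen analysis plan could also add covariates and contrasts. What remains is that the article does fix an unadjusted one-way ANOVA and a wrong model name, and both can be corrected in its text.
- **A larger power gap is tempting but mixes causes.** At ρ = 0.5, take a difference of 0.634 SD (from the t distribution), IAT halfway between the other arms, and compound symmetry with a constant effect over four windows. The adjusted CAT–sham contrast then has 80% power, against 56% for an 8-df interaction and 57% for the unadjusted three-arm test. But a baseline-adjusted three-arm test has only 70%, so 10 of the 23 points between 80% and 57% come from testing three arms at once. Placing IAT halfway is also unfavourable: if IAT equals either other arm, the interaction has 71% and the unadjusted three-arm test 70%. The 8 df assume five time levels that the article does not fix.
- **Mann–Whitney.** A reader might infer that a two-group test is misapplied to three arms. The sentence begins "Comparisons of categorical data among groups will be examined using" and does not present it as a single three-arm test. Pairwise use fits the wording, and the sentence on the three groups refers to non-parametric tests generally.

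**Conclusion.** Two things hold. The term one-way is wrong for a model meant to give group and time-by-group effects, and should be replaced. The stated between-arm test leaves the baseline VAS unused, at a cost in precision only.

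The size of that cost rests on the assumed ρ of 0.3 to 0.6: 9% to 36% of the variance, or about 4 to 19 points of pairwise power at an effect that the adjusted contrast detects with 80% power. Because entry is restricted to 3 < VAS < 7, ρ may be low and the gain near the lower end. The power figures are for one contrast at two-sided 0.05; at ρ = 0.5, splitting alpha over two contrasts by Bonferroni would bring the adjusted CAT–sham power from 80% to 71%.

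This is a moderate point: worth correcting, but not a flaw that invalidates the analysis.

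**What to change.** In the Clinical data analysis section, replace both stated methods for the VAS with one baseline-adjusted model for the post-baseline scores. Either of these would do:

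- ANCOVA at the primary window, with arm and baseline VAS; or
- a linear mixed model with arm, window, arm by window and baseline VAS.

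Name the primary window in the same sentence. The Secondary outcomes section lists VAS for weeks 8–16 as secondary, which suggests that the primary window ends at week 8, but the authors should confirm this. Report CAT minus sham CAT and CAT minus IAT at that window, each with a 95% confidence interval, since these are the comparisons in the first aim.

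The cost is a few lines of text and a small change to the analysis. Baseline VAS is already collected, and no visit, procedure or patient is added. The change should be made before unblinded data are examined.

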### Neuroimaging data analysis

The structural MRI data will be analyzed using the VBM toolbox within SPM12. The steps will include interlaminar time difference correction, spatial difference correction, head motion correction, normalization, and Gaussian smoothing (Yao et al., 2021). During head motion correction, images of participants with translations of less than 1 mm and rotational movements of less than 2° will be involved in the subsequent analysis. The MRI data will be analyzed using PANDA, GRETNA and BrainNet Viewer toolboxes and SurfStat. In VBM analysis, generalized linear regression model analysis will be used and between-group VBM comparisons will be made using corrected subject migraine attack intensity, migraine attack frequency, etc. (control covariates: age, PSQI, SAS, SDS, etc.) and total intracranial volume by two-sample *t*-test. A significant difference between groups will be indicated when *p* < 0.05 (FWE corrected). Only collections with more than 20 voxels will be considered as statistically significant brain regions. First, the FC of PAG in the baseline session will be compared between the migraine patients and normal participants using two sample *t*-test with FWE correction. Second, two-factor three-level mixed design ANOVA (Time: baseline and after treatment; Treatment: CAT, IAT, and sham CAT) will be conducted on migraine patients to explore the effect of treatment schedule on the FC of PAG after FWE correction. *Post hoc* analysis will be implemented using paired *t*-test to investigate the alteration of FC between before and after treatment for each treatment schedule. Finally, Pearson correlation analysis will be performed between the change in VAS score and the changes of FC in significant regions for three treatment schedules, respectively. The statistical analysis for the VBM will follow a similar procedure to that for the FC of PAG.

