#### Secondary outcomes

Secondary outcomes include migraine attack frequency per month (−4 to 16 weeks), migraine attack days per month (−4 to 16 weeks), migraine attack intensity VAS score (8–16 weeks), duration of migraine (−4 to 16 weeks), emergency medication intake dose (−4 to 16 weeks), Migraine-Specific Quality of Life Questionnaire (MSQ) (−4 to 16 weeks), Migraine Disability Assessment Score (MIDAS) (−4 to 16 weeks), Headache Impact Test-6 (HIT6) (−4 to 16 weeks), Pittsburgh Sleep Quality Index (PSQI) (−4 to 16 weeks), Self-Rating Anxiety Scale (SAS) (−4 to 16 weeks), and Self-Rating Depression Scale (SDS), which are closely related to migraine. Blinding/reliability assessments will be conducted at the end of treatment (week 8) (Supplementary File 5), and treatment adherence evaluation will be assessed at the end of the follow-up period (week 16).

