### Voxel-base morphometry analysis

The gray matter volume (GMV) will be calculated using voxel-base morphometry (VBM) analysis in the FMRIB software library (FSL) (Jenkinson et al., 2012) version 5.0.9.^1^ First, all T1-weighted data will undergo brain extraction using the Brain Extraction Tool (BET) (Smith, 2002) and will be visually checked by an experienced neurologist to remove any leftover non-brain tissue. Second, using the FMRIB’s Automated Segmentation Tool (FAST) (Smith, 2002), the obtained brain-extracted data will be segmented into gray matter (GM), white matter (WM), and cerebrospinal fluid (CSF). Third, the resulting GM images were non-linearly registered to the GM ICBM-152 template using the non-linear registration tool FNIRT, and then averaged and flipped along the x-axis to obtain a first-pass, study-specific GM template. Next, the native segmented GM images will be nonlinearly re-registered to the above GM template and averaged to generate the final symmetric, study-specific GM template. Furthermore, the registered GM images will undergo modulation using the Jacobian of the warp field to produce maps of GMV. Finally, the obtained GMV images will be smoothed with a Gaussian kernel of 3 mm (a full-width half-maximum of ∼7 mm).

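### The baseline patient-versus-control grey-matter comparison appears to be corrected for attack intensity and frequency, which nearly duplicate group membership; the VBM pipeline is also described in two conflicting ways

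*Protocol article*

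**What the plan says.** The Neuroimaging data analysis section describes a regression model for VBM in which "between-group VBM comparisons will be made using corrected subject migraine attack intensity, migraine attack frequency, etc", followed by a bracket reading "control covariates: age, PSQI, SAS, SDS, etc" and then total intracranial volume, all by two-sample t-test. That sentence names neither the groups nor the time at which the covariates are measured.

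The groups can be inferred from the text that follows. For PAG connectivity, the baseline session is "compared between the migraine patients and normal participants using two sample" t-tests, the treatment arms are handled by a Time by Treatment mixed ANOVA, and the section closes with "The statistical analysis for the VBM will follow a similar procedure to that for the FC of PAG".

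The migraine variables are trial outcomes. Under Primary outcome, "the primary outcome is the intensity of the migraine attack, which will be assessed using a VAS score of 0–10"; under the next heading, "Secondary outcomes include migraine attack frequency per month", with PSQI, SAS and SDS in the same list. The Discussion gives a reason for using the psychological scales: to keep anxiety and depression from confounding the results.

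On the pipeline, the Voxel-base morphometry analysis section computes grey-matter volume by "voxel-base morphometry (VBM) analysis in the FMRIB software library (FSL"), with BET, FAST and FNIRT. The Neuroimaging data analysis section says "The structural MRI data will be analyzed using the VBM toolbox within SPM12", and its steps include slice-timing and head-motion correction with limits of 1 mm and 2°.

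**The concern.** Attack intensity and frequency are features of the disease that separates the two groups. No control can have a patient's value and no eligible patient can have a control's value. In a model holding both group and these covariates, the controls, all at one value, say nothing about the slope. The slope comes from patients alone, and the group coefficient becomes the patient regression line extended down to VAS 0, minus the control mean. That contrast concerns a migraine patient without migraine, whom the eligibility criteria exclude. A real grey-matter difference could then be reported as absent.

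Two further matters sit in the same text. The covariates have no time point and both lists are open-ended, so post-treatment values are not ruled out if the covariates are carried into the arm comparison. And two software routes for one analysis leave a choice that could be made after the maps have been seen.

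**Working it through.** **The plan's own figures.** The protocol gives no effect size, variance or power for VBM, so there is no VBM figure to reproduce. Its group sizes are the inputs. From the Sample size calculation section, 30 per arm with 8% loss gives 30/0.92 = 32.6 or 30 × 1.08 = 32.4, stated as 32; 3 × 32 = 96 patients, plus 30 controls.

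**Inputs from the documents.** Patients: VAS strictly between 3 and 7, at least 2 attacks a month, fewer than 15 headache days a month. Controls: no neurological disorder.

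**Assumptions, not in the documents.** Controls coded 0 on both variables. Patient VAS mean 5; SD 1.15 (uniform on 3 to 7: 4/√12), 1.0 or 0.8.

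**Intensity alone.** With control share p = 30/126 = 0.238, the variance of VAS splits into:
- between groups: p(1 − p) × 5² = 0.1814 × 25 = 4.535
- within groups: (1 − p) × SD² = 0.762 × SD²

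R² = between / (between + within), VIF = 1/(1 − R²), and the standard error grows by √VIF.

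| Patient SD | Within | R² | VIF | SE multiplier |
|---|---|---|---|---|
| 1.15 | 1.016 | 0.82 | 5.5 | 2.3 |
| 1.0 | 0.762 | 0.86 | 6.95 | 2.6 |
| 0.8 | 0.488 | 0.90 | 10.3 | 3.2 |

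**Intensity and frequency together.** These are simulated, with 96 patients, 30 controls and 2,000 replicates per scenario. With VAS uniform on 3 to 7 and attacks uniform from 2 up to 6, 8 or 14 a month, VIF is 6.9 to 8.5. If VAS is concentrated on 4 to 6 (attacks 2 to 6), VIF is about 22.

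**Effect on the result.** Assume a true unadjusted difference of 0.6 SD and nominal two-sided 0.05 without FWE correction. Unadjusted, SE = √(1/96 + 1/30) = 0.209, 0.6/0.209 = 2.87, and power is Φ(2.87 − 1.96) = 0.82; simulation gives 0.80 to 0.82. With both migraine variables in the model:
- *Grey matter proportional to intensity:* the adjusted difference is −0.02 to 0.02 and the rejection rate 0.04 to 0.05.
- *Pure step between groups:* the estimate stays at 0.59 to 0.62, but power is 0.17 to 0.19 with VAS on 3 to 7 and 0.09 on 4 to 6. By hand, at VIF 7.65 the SE is 0.209 × 2.77 = 0.579, 0.6/0.579 = 1.04, and Φ(1.04 − 1.96) = 0.18.

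**PSQI, SAS and SDS.** With an assumed shift of 0.5 SD between patients and controls on each scale, the VIF for group is 1.17.

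**Randomised arms.** Simulated at 32 versus 32, 4,000 replicates, with an arm effect of 0.60 running wholly through symptom change: 0.60 unadjusted, 0.60 with the baseline covariate, −0.01 once the post-treatment value is added.

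**Pipeline.** The MRI data section describes the T1 scan as one three-dimensional structural acquisition and the resting-state scan as 210 volumes at TR 2 s (420 s, or 7 min). Slice-timing and volume-to-volume motion correction apply to the second. As placed, the 1 mm and 2° limits would decide inclusion in a structural analysis that yields no such motion estimates.

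**The case against.** The covariate sentence is badly worded. Intensity and frequency stand outside the bracket labelled as control covariates, so they might be regressors of interest. That is possible, but the word for correction attached to them points the other way, and the ambiguity itself needs settling.

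A reader might infer more: that all five outcome variables are improper covariates and that the model removes the treatment effect. The documents do not support this. The two-sample wording belongs to patients versus controls at baseline; the arms go to a mixed ANOVA, for which no covariates are stated. Baseline values leave a randomised comparison intact, and the harm appears only with post-treatment values, which the text neither states nor excludes. Baseline PSQI, SAS and SDS are a defensible adjustment for patients versus controls, the Discussion gives the reason, and they cause little collinearity. Nor is the effect always removed: under a pure step, only precision is lost.

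The sizes also depend on assumptions. The protocol does not say what value a control would receive for intensity or frequency, although leaving it undefined would make the model unfittable for controls.

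The slice-timing and motion steps may simply be misplaced resting-state text, and further preprocessing is in Supplementary File 6, which is not shown. That may explain the steps, but it does not reconcile FSL with SPM12 in the article itself.

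**Conclusion.** The point holds for one comparison. On the most natural reading, the baseline patient-control VBM test is corrected for two variables that nearly define its groups. Intensity alone gives a VIF of about 5.5 to 10 and a standard error about 2.3 to 3.2 times larger, given controls coded 0, mean VAS 5 and SD from 1.15 down to 0.8. The adjusted difference is then either near zero or unbiased with power of roughly 0.1 to 0.2 instead of 0.8, the power figures resting also on the assumed 0.6 SD difference. For the randomised arms there is a gap to close, not a demonstrated bias. The FSL and SPM12 descriptions contradict each other whatever is assumed. Severity is moderate: VBM supports the second, mechanistic aim, while the primary outcome is clinical and the stated PAG connectivity tests carry no such covariates.

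**What to change.** 1. Remove attack intensity and attack frequency from the patient-control VBM model. Relate them to grey-matter volume in a separate analysis within patients.
2. Keep age and total intracranial volume in that model and, if wanted for the confounding reason in the Discussion, baseline PSQI, SAS and SDS, provided that controls also complete these scales.
3. State that any covariate used in a comparison between randomised arms is a baseline value.
4. Replace the open-ended lists with a closed list of covariates and their time points, and name the groups in the two-sample sentence.
5. Name one VBM pipeline in both sections. Move slice-timing correction, head-motion correction and the 1 mm and 2° limits to the resting-state analysis.

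The cost is wording, settled before the imaging data are analysed. No change to recruitment, scanning or sample size is needed.

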### Participants

#### Inclusion criteria for patients with MWoA

(i) Meeting the diagnostic criteria for MWoA in the International Classification of Headache Disorders (ICHD-3) (Bes et al., 2018); (ii) right handed, female, high school or above education, aged 18–45 years old; (iii) in the past 3 months, the headache attack was ≥2 times per month, and the headache days were <15 days per month; (iv) moderate headache attacks (3 < visual analog scale (VAS) score < 7) (Lee et al., 2016) in the last 4 weeks (baseline period); (v) history of migraine for more than 1 year and no history of dysmenorrhea; (vi) no acupuncture or pharmacological treatment within 1 month; (vii) no metallic implants in the body and no MRI contraindications; and (viii) not participating in any other trials during the study period and signing a written informed consent form.

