#### Inclusion criteria for HCs

(i) Right handed, female, high school education or above, aged 18–45 years; (ii) no history of prolonged dysmenorrhoea, no neurological or psychiatric disorders, and no family history of a genetic predisposition; (iii) absence of physical abnormalities (e.g., cold, fever, etc.) during the trial; (iv) no medication or alcohol consumption at least 2 days prior to enrollment, and no use of stimulants for at least 1 month; and (v) willingness to participate and the ability to sign the informed consent form.

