### MRI data

Magnetic resonance imaging data will be acquired within 1 week before the treatment and within 1 week after 8 weeks of treatment. The MRI will be acquired to avoid the patient’s migraine attacks, and all migraine patients should be without migraine (intermittent) for at least 72 h prior to the MRI scan before the scan is performed. Otherwise, the scan will be rescheduled. A Magnetic Resonance Scanner (3.0T GE Discovery 750; Milwaukee, WI, USA) with a 16-channel phased array head coil will be used, along with a restraining foam pad to minimize head motion and diminish scanner noise. The scans will be conducted at the Department of Radiology, the First Affiliated Hospital of Kunming Medical. Three-dimensional T1-weighted structural images will be obtained with the following scanning parameters: repetition time (TR) = 8.2 ms; echo time (TE) = 3.18 ms; field of view (FOV) = 256 mm × 256 mm; matrix = 512 × 512; in-plane resolution = 0.5 mm × 0.5 mm; slice thickness = 1 mm; 196 sagittal slices; flip angle = 9°. Resting-state functional MRI (rsfMRI) data will be collected within 7 min using the following parameters: TR = 2 s; TE = 30 ms; FOV = 240 mm × 240 mm; matrix = 64 × 64; in-plane resolution = 3.75 mm × 3.75 mm; slice thickness = 3.5 mm; 45 axial slices; flip angle = 90°, and 210 volumes will be acquired for each participant. Additional MRI data acquisition and preprocessing methods and procedures are described in Supplementary File 6.

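### The baseline patient-versus-control PAG connectivity comparison is set as a t-test with no covariate, although age may differ between these non-randomised groups and is a named covariate for VBM

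*Protocol article*

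**What the plan says.** Three parts of the protocol article bear on this.

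- **The connectivity test.** Under Neuroimaging data analysis, the first step is that "the FC of PAG in the baseline session will be compared between the migraine patients and normal participants". The method named is a two-sample t-test, with family-wise error (FWE) correction. No covariate is attached to it.
- **The sister analysis.** Earlier in that section, the between-group VBM comparison is adjusted for total intracranial volume and clinical variables, with "control covariates: age, PSQI, SAS, SDS, etc". The section closes with "The statistical analysis for the VBM will follow a similar procedure to that for the FC of PAG". That sentence carries the connectivity procedure over to VBM. It does not carry the VBM covariates over to connectivity.
- **The groups.** Randomization and blinding covers the migraine patients only. Patients must be "right handed, female, high school or above education, aged 18–45 years old" and controls "Right handed, female, high school education or above, aged 18–45 years". No individual or frequency matching within those limits is described.

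On head motion, the section includes motion correction and states that "images of participants with translations of less than 1 mm and rotational movements of less than 2° will be involved in the subsequent analysis". Elsewhere, under the heading MRI data, the article adds that "Additional MRI data acquisition and preprocessing methods and procedures are described in Supplementary File 6", a file that is not shown.

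**The concern.** A two-sample t-test attributes the whole mean difference to group. That is safe when randomisation balances everything else, but here the 30 controls are a separately recruited sample. Common eligibility limits fix sex and handedness and set a floor on education. They leave age free over 27 years. If connectivity varies with age and the two groups differ in mean age, the test reports a difference that has nothing to do with migraine. The bias can also run the other way and hide a real one. FWE correction controls the number of false findings across the brain when the null model is right; it does nothing about a systematic shift between groups.

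The contrast matters for interpretation. The abstract hypothesises that contralateral acupuncture works by reversing abnormal brain activity with the PAG at its core, and the second aim in the Introduction concerns a migraine pathology network. Comparison with healthy controls is the only planned connectivity analysis that can show which PAG connections are abnormal. Without a sound answer there, a change under treatment is only a change and cannot be called restoration.

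**Working it through.** **Is there a figure in the plan to reproduce?** Not for this contrast. The sample size section gives 30 per group, inflated for 8% loss to 32 (30/0.92 = 32.6), hence 96 patients, and 30 controls. No effect size, SD or power is stated. The group sizes are all that is needed below.

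**Inputs from the document.** 96 patients and 30 controls. The seed-based FC section restricts the analysis to those who complete the trial, which at 8% loss is about 88 to 90 patients (96 × 0.92 = 88.3; 3 × 30 = 90).

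**Inputs assumed.** The within-group correlation r between the covariate and connectivity, and the gap Δ between group means in SD units of the covariate. Neither is in the document, so a range is shown.

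**Is a gap of this order possible?** If ages were uniform over 18–45, the SD would be 27/√12 = 7.8 years. A gap of 0.5 SD is then about 4 years, which the eligibility limits permit.

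**Formula.** With no true migraine effect, the spurious standardised difference is d = r × Δ. The standard error with 96 v 30 is √(1/96 + 1/30) = 0.209. The noncentrality is d/0.209.

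Example: r = 0.3 and Δ = 0.5 give d = 0.15 and noncentrality 0.15/0.209 = 0.717. By the normal approximation, two-sided rejection at 1.96 is P(Z > 1.243) + P(Z < −2.677) = 0.107 + 0.004 = 0.111. The same sum gives 7.7% at d = 0.10 and 16.0% at d = 0.20.

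**Range** (noncentral t, 96 v 30, one location, nominal two-sided 5%):

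| r | Δ = 0.25 | Δ = 0.5 | Δ = 0.75 | Δ = 1.0 |
|---|---|---|---|---|
| 0.1 | 5.2% | 5.6% | 6.5% | 7.6% |
| 0.2 | 5.6% | 7.6% | 11.0% | 15.8% |
| 0.3 | 6.5% | 11.0% | 18.7% | 29.6% |
| 0.4 | 7.6% | 15.8% | 29.6% | 47.5% |

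With 90 v 30 the values are almost the same (10.9% at r = 0.3, Δ = 0.5).

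**Does adjustment remove it?** In 20,000 simulated trials per setting with r = 0.3, the unadjusted test rejected in 10.7% (Δ = 0.5) and 19.1% (Δ = 0.75). With the covariate in a linear model the rates were 4.7% and 5.0%.

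**The case against.** The strongest reply is that the article is silent on connectivity covariates and does not exclude them. The adjusted VBM comparison is itself described as a two-sample t-test, so the authors may use that phrase for an adjusted contrast, and covariate lists are often left to a fuller document. This has some force as to intent. But the article does state the test for connectivity, and it does list covariates for VBM in the same section. A reader who follows the text would adjust one and not the other.

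The second reply is that every magnitude above is assumed. That stands. The figures illustrate the mechanism and do not estimate the bias in this trial. They also refer to one location at nominal 5%, so the 11% should not be read as the error rate of the FWE-corrected map.

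A reader might also infer more than the document supports:

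- **That the groups are simply unmatched.** They share restrictions on sex, handedness, minimum education and age range. Both also exclude smoking or alcohol addiction and MRI contraindications, and both are recruited from the same hospital and the Kunming communities. What is missing is balance on age within the range.
- **That head motion is uncontrolled.** Motion correction and a 1 mm / 2° limit are stated, and Supplementary File 6 may add motion regression. Only residual motion below the limit is open, and only if that file does not cover it.
- **That confounding passes into every later imaging result.** The PAG seed is fixed in advance from published coordinates. The Time × Treatment ANOVA uses randomised patients only, and no mask from the control comparison is stated. The paired tests and the correlations with VAS change are within patients. The most that can be said is that the source of the significant regions used for those correlations is not spelled out.

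**Conclusion.** The point holds in a limited form. As written, the baseline PAG connectivity contrast between migraine patients and healthy controls takes no account of age, while the VBM contrast beside it does. The groups are restricted alike but are neither randomised against each other nor matched on age, so an age difference could pass for migraine pathology.

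The size cannot be derived from the document. Over assumed correlations of 0.1 to 0.4 and gaps of 0.25 to 1 SD, the single-test error runs from about 5% to 47%; at r = 0.3 and 0.5 SD it is about 11%. If the groups turn out close in age, the effect is negligible.

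The consequence is confined to the statement of which PAG connections are abnormal at baseline, and to describing any treatment change as restoration. The randomised comparisons and the primary VAS outcome do not use the controls and are untouched. The change is still worth making, because it costs almost nothing and removes the bias from age to the extent that the model for age is right.

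**What to change.** Replace the baseline two-sample t-test with a linear model for connectivity with group (patient v healthy control) and age as terms, keeping the same FWE correction. Add each participant's mean head motion as a further term if Supplementary File 6 does not already deal with residual motion. State in one sentence which covariates apply to connectivity and which to VBM, so that the closing cross-reference between the two is unambiguous. The Time × Treatment model needs no change on this account.

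Age is an eligibility item for both groups and so is held for everyone. A motion summary follows from the motion correction already planned. The cost is one or two degrees of freedom out of about 120 (124 with 96 v 30; 118 with 90 v 30), and the wording. Frequency-matching controls on age would also help if recruitment is still open, but it takes recruitment effort and is not needed for the fix. Years of education are not proposed as a covariate, because the article shows education only as an eligibility threshold.
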